**Study Name: RESILIENCE: Research for pErSonalized cardIovascular dIsease prEvention, treatmeNt, and CarE.**

**Study Sponsor: Duke University – Translating Duke Health Initiative**

**Protocol Author: [name] MPH**

### Protocol Synopsis:

- **Background/Rationale:** Obesity is a rapidly growing epidemic that is associated with the development of cardiovascular disease (CVD). However, obesity is a heterogeneous disease; while some develop CVD early, others appear to be CVD resistant. Similarly, responses to weight loss interventions in obese individual are also quite variable. While some lose weight and improve CVD risk factors, demonstrating apparent resilience to obesity and CVD risk, others are non-responsive to interventions.
- **Objectives/Hypotheses:** Our overall objective is to understand factors contributing to the heterogeneity of CVD resistance and resilience among individuals with obesity at Duke. A secondary objective is to determine optimal methods of recruiting and consenting patients for clinical studies.
- **Study Design:** The RESILIENCE study is a prospective study that will be conducted with 600 patients within the Duke Health System. We aim to recruit patients with 4 phenotypes: 200 patients with obesity (BMI  $\geq 30$ ) and high 10-year ASCVD risk ( $\geq 20\%$ ), 200 patients with obesity (BMI  $\geq 30$ ) and low 10-year ASCVD risk ( $< 7.5\%$ ), 100 patients with normal weight (BMI 18-25) and high 10-year ASCVD risk ( $\geq 20\%$ ), and 100 patients with normal weight (BMI 18-25) and low 10-year ASCVD risk ( $< 7.5\%$ ). Clinical, behavioral, and molecular characteristics will be compared at baseline between the 4 groups to understand heterogeneity between obesity and risk for CVD. Patients with obesity will undergo a 6-month weight loss intervention. Clinical, behavioral, and molecular characteristics will be compared between baseline and 6 months to understand (a) predictors of response to the intervention and (b) how these factors change with weight loss. To address the secondary objective listed above, we will test recruitment strategies using a 2x2 factorial design that will randomize individuals, stratified by phenotype above, to personal email vs. MyChart message, and to different message content. We will also test consenting strategies by randomizing individuals, again stratified by phenotype above, to 1 of 4 informed consent formats: text only, text + physician video, text + patient video, text + animated video.
- **Study Population:** The study population will consist of adult patients who receive care in the Duke Health System, and who fall into 1 of 4 phenotypes: 200 patients with obesity (BMI  $\geq 30$ ) and high 10-year ASCVD risk ( $\geq 20\%$ ), 200 patients with obesity (BMI  $\geq 30$ ) and low 10-year ASCVD risk ( $< 7.5\%$ ), 100 patients with normal weight (BMI 18-25) and high 10-year ASCVD risk ( $\geq 20\%$ ), and 100 patients with normal weight (BMI 18-25) and low 10-year ASCVD risk ( $< 7.5\%$ ). Potentially eligible patients will be identified using Duke Electronic Health Record (EHR) data, with additional inclusion and exclusion criteria.
- **Exposure(s):** Individuals with obesity will undergo a 6-month weight loss intervention called TRACK, which is a digital behavioral intervention involving text messaging, phone-based coaching, and digital scales; it has been proven to lead to significant weight loss.
- **Outcome(s):** Differences in branched-chain amino acids will be compared between all groups, both at baseline and at 6 months (for those patients undergoing the TRACK intervention). Other clinical, behavioral, metabolomic, genetic, and microbiome parameters will also be compared in an exploratory fashion.

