#### 1.2 Rationale

Understanding heterogeneity in weight loss and accompanying changes in CVD risk profiles at both epidemiological and biological levels is critical to providing personalized obesity care and to promoting CV health. In order to develop a complete picture of CVD resistance and resilience in obesity, we need to integrate all potential predictors to create a detailed map of individual clinical, behavioral, and molecular changes that occur in obesity. As recently advocated for by the National Institutes of Health in *JAMA*, this requires phenotyping large numbers of patients clinically, behaviorally, and physiologically, and integrating all of these data. Unfortunately, very few such data sources currently exist.

To accomplish this goal, we will identify a heterogeneous cohort of obese and normal BMI patients with high or low 10-year risk for CVD (i.e. >30% or <10%). We will then remotely collect data using electronic consents, electronic health record (EHR) clinical data, and online behavioral surveys. Further, we will collect biological data remotely with home biospecimen kits. Remote collection will reduce participant burden, increase participation and retention, and potentially reduce costs.

This platform will enable us to understand which clinical, behavioral, and biological markers are related to high-risk obese individuals vs. “resistant” low-risk obese and high-risk normal BMI individuals. Then, we will embed within this cohort a digital health behavioral intervention called TRACK. This will enable us to identify which clinical, behavioral, and biological markers change with weight loss, as well as which markers predict degree of weight loss and improvement in cardiometabolic risk factors (“resilience”).

One promising marker that we will specifically evaluate is branched chain amino acids (BCAA), which have previously been associated with insulin resistance in obese patients. We will assess whether BCAA are associated with CVD risk more strongly in obese compared with normal BMI patients, and whether BCAA predict response to a weight loss intervention. We will also perform metabolomic, genetic, and microbiome profiling for discovery science.

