### **2.1. Primary Aims & Hypotheses**

Aim 1: CVD Resistance in Obesity. We aim to understand the clinical, behavioral, and biological factors associated with obesity and CVD risk by understanding differences between obese vs. normal BMI and high vs. low CVD risk groups. To do this, we will develop a cohort of obese and normal BMI patients at high and low CVD risk (n=600), and will deeply phenotype these individuals with behavioral data and biospecimen collection. Half (n=300) will also undergo CT testing to determine coronary artery calcium (CAC) score, for validation of the above associations. Finally, an embedded mechanistic study (n= 40) will explore the effect of the identified markers on vascular endothelial function.

Hypothesis 1a: BCAA are associated with CVD risk in obese individuals more than in normal BMI individuals in a real-world population, and this association will be validated with CAC score.

Hypothesis 1b: Specific clinical, behavioral, metabolomic, genetic, and microbiome profiles will be associated with CVD risk in obese individuals more than in normal BMI individuals.

Hypothesis 1c: In tissue-engineered blood vessels, BCAA interact with lipoproteins to induce endothelial dysfunction and increased monocyte/macrophage accumulation in the arterial wall, which are early markers of atherosclerosis.

Aim 2: CVD and Obesity Resilience. We will implement a proven, digital health behavioral intervention with 400 deeply phenotyped obese individuals in our cohort. We will then explore clinical, behavioral, and biological factors associated with heterogeneity in response to this intervention. Response will be defined as (1) weight loss and (2) changes in CVD risk factors, including LDL-cholesterol, HbA1c, Homeostasis model assessment for insulin resistance (HOMA), and hs-CRP.

Hypothesis 2a: Baseline clinical, behavioral, and/or biological markers, and specifically BCAA, will predict response to the intervention.

Hypothesis 2b: Biological markers, including BCAA and other markers discovered through integrated - omics analysis, will change from baseline with weight loss and changes in CVD risk factors.

Hypothesis 2c: Obese individuals with high CVD risk who lose weight with the intervention will develop biological profiles more similar to normal BMI, low CVD risk individuals.

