Clinical, behavioral, and molecular characteristics will be compared at baseline between the 4 groups to address Aim 1. Among patients with obesity, clinical, behavioral, and molecular characteristics will be compared between baseline and 6 months to understand (a) predictors of response to the intervention and (b) how these factors change with weight loss (Aim 2).

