## **8.3 BCAA Analysis**

### **8.3.1 Sample Size Calculation:**

Based on effect sizes from our previous studies of the BCAA signature of a difference in mean (SD) levels between the two groups of 0.32 (0.95), a sample size of 109 in each group would provide 80% power, indicating that we should have enough power to perform this primary analysis.

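### Hypothesis 1a is an obesity-by-risk interaction in BCAA, but no stated analysis tests it, and the sample size in protocol 8.3.1 is for an unidentified two-group difference

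*Combined protocol and SAP*

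**What the plan says.** The question is put clearly in two places. Hypothesis 1a (protocol 2.1) is that "BCAA are associated with CVD risk in obese individuals more than in normal BMI individuals in a real-world population", and the Rationale (1.2) repeats it: "We will assess whether BCAA are associated with CVD risk more strongly in obese compared with normal BMI patients".

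The analysis is described only in general terms. The Protocol Synopsis, under outcomes, has "Differences in branched-chain amino acids will be compared between all groups, both at baseline and at 6 months". Section 3.1 has "Clinical, behavioral, and molecular characteristics will be compared at baseline between the 4 groups to address Aim 1". The planned groups are 200 obese high risk, 200 obese low risk, 100 normal-weight high risk and 100 normal-weight low risk.

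Section 8.3, on the BCAA analysis, holds nothing but a sample-size paragraph (8.3.1). It cites "a difference in mean (SD) levels between the two groups of 0.32 (0.95" (the second figure being the SD), says that "a sample size of 109 in each group would provide 80% power", and concludes that "we should have enough power to perform this primary analysis". The two groups are not named, and the analysis called primary is not defined anywhere else. No model, test, alpha, sidedness or multiplicity rule is given for BCAA. The alpha rule in 8.1 is for the recruitment sub-study and is carried over only to the consent sub-study in 8.2. The SAP covers Aim 4 alone.

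**The concern.** A claim that an association is stronger in one class than in another is a claim about a difference of differences: (obese high − obese low) − (lean high − lean low). No two-group comparison can answer it. An overall comparison of four groups does not isolate it either, since a plain BCAA difference between obese and lean people would make such a comparison significant with no interaction at all.

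BCAA is not one of the exploratory measures. The synopsis sets it apart from the other parameters, so a deciding test is to be expected. Two things are at stake. First, the analyst may choose after seeing the data which contrast counts as support for Hypothesis 1a, and one available choice (significant in the obese, not significant in the lean) is a poor guide to whether the associations differ. Second, 8.3.1 assures the reader of adequate power for a comparison that is not the one in the hypothesis.

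**Working it through.** **Inputs.** Difference 0.32 and SD 0.95 (8.3.1); group sizes 200/200/100/100 (synopsis, 3.1). Alpha and sidedness are not stated for BCAA. I assume two-sided 0.05 and show one-sided 0.05 as the alternative. Normal approximation, same SD in all groups.

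**1. The plan's own figure.** n per group = 2 × (SD/difference)² × (z_alpha + z_power)².
- One-sided 0.05: 2 × (0.95/0.32)² × (1.645 + 0.842)² = 109, as stated.
- Two-sided 0.05: 2 × (0.95/0.32)² × (1.960 + 0.842)² = 139. With 109 per group, two-sided power is 70%.

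So 109 is reproduced only by a one-sided 0.05 test that the protocol does not mention. Each lean group (100) also falls short of 109: power for lean high v low risk is 77% one-sided and 66% two-sided.

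**2. Separate tests in each class, Hypothesis 1a false.** Let the true gap be 0.32 in both classes. Power = Φ(gap/SE − z), with SE = 0.95 × √(2/n).
- Obese, n = 200: SE = 0.0950; Φ(3.368 − 1.960) = 0.920.
- Lean, n = 100: SE = 0.1344; Φ(2.382 − 1.960) = 0.663.
- P(obese significant, lean not) = 0.920 × (1 − 0.663) = 0.31.
- P(lean significant, obese not) = 0.663 × (1 − 0.920) = 0.05.
- One-sided 0.05: 0.958 × (1 − 0.769) = 0.22.

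P(obese significant, lean not) for other equal gaps:

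| True gap in both classes | 200/100 per group, two-sided | 200/100 per group, one-sided | 150/150 per group, two-sided |
|---|---|---|---|
| 0.10 | 16% | 23% | 13% |
| 0.20 | 38% | 38% | 25% |
| 0.24 | 41% | 36% | 24% |
| 0.32 | 31% | 22% | 14% |
| 0.40 | 15% | 9% | 4% |
| 0.50 | 4% | 2% | 0.5% |

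The last column keeps the total at 600 with equal groups. At a gap of 0.32, the 2:1 split raises the figure from 14% to 31%. Equal groups of 100 give 22% and equal groups of 200 give 7%. Unequal size therefore makes the problem worse, but comparing significance across classes is what creates it.

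**3. The interaction test.** SE = 0.95 × √(1/200 + 1/200 + 1/100 + 1/100) = 0.1645.
- The false-positive rate is the chosen alpha: 5% two-sided, of which 2.5% lies in the hypothesised direction.
- Power for a difference of differences of 0.32: Φ(0.32/0.1645 − 1.960) = 49% two-sided; Φ(0.32/0.1645 − 1.645) = 62% one-sided.
- Detectable with 80% power: 0.1645 × (1.960 + 0.842) = 0.46 two-sided; 0.1645 × (1.645 + 0.842) = 0.41 one-sided.
- For 80% two-sided power at 0.32 with the 2:1 ratio kept: 3 × (0.95 × 2.802/0.32)², or about 208 per lean group, and so 416 per obese group.

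**The case against.** The strongest reply is that the protocol asks the right question. Sections 1.2 and 2.1 both pose it as a comparison of associations, and an analyst who follows that wording would fit an interaction. Nothing says that Hypothesis 1a will be read by setting one p-value beside another. That stands. A reader might infer that the plan intends separate within-class tests and so carries a 31% false-confirmation rate. The documents do not support this: they allow that reading and do not choose it. The 31% also depends on a gap of 0.32 in both classes and on two-sided 0.05; under the one-sided 0.05 that reproduces 109, it is 22%. Nor can it be put down to the obese groups being twice as large, since equal groups still give 14% at the same total.

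A reader might also infer that comparing all groups means six pairwise tests. Unadjusted at two-sided 0.05, with all four means equal, these have a family error of about 20% (by simulation with 200/200/100/100). The documents do not say that six tests will be run or that they will be unadjusted; one global test or adjusted pairs would fit the wording equally well. Most of the six pairs would not bear on Hypothesis 1a anyway, so 20% is not its error rate.

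What the reply does not remove is the omission. Section 8.3 is the only place for the BCAA analysis, and the one comparison sized there is a two-group difference. The SAP shows that the device was familiar: for Aim 4, sections 9.3 and 10.3 specify interaction terms outright.

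**Conclusion.** The point holds as an unspecified deciding analysis. Hypothesis 1a is an interaction, the stated analyses do not test it, and the power statement in 8.3.1 belongs to a different and unnamed comparison. This follows from the text alone.

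The sizes are conditional. The separate-tests figure (31% two-sided, 22% one-sided, about 4% to 41% two-sided over gaps of 0.10 to 0.50) illustrates what the silence permits; it is not an error rate of a stated plan. The interaction's power, 49% two-sided or 62% one-sided, rests on SD 0.95 in every group, the full planned numbers, and taking 0.32 as the difference of differences. The protocol gives no value for that last quantity. A true interaction smaller than the within-class gap would be harder still to detect.

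**What to change.** In protocol 8.3, state that Hypothesis 1a is decided by the obesity × risk-group interaction on baseline BCAA in all 600 participants, at a stated alpha and sidedness. State that within-class and other pairwise differences are descriptive, reported with confidence intervals, and that significance in one BMI class but not in the other is not taken as evidence for Hypothesis 1a.

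In 8.3.1, name the two groups to which 109 per group refers, and say that the figure does not apply to the interaction. Simply making the interaction the primary analysis while keeping 109 and 80% would produce a false power statement. Disclose instead that with 200/200/100/100 the interaction has about 49% power two-sided (62% one-sided) for a difference of differences of 0.32, and reaches 80% only at about 0.46 (0.41 one-sided).

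The cost is wording and one model term, with no new data. The downside is that the stated power for the deciding test becomes less favourable, and a non-significant interaction would have to be read as inconclusive rather than as evidence of equal associations.

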## Protocol:

### 1. Background and Rationale

#### 1.1 Background

Obesity is a rapidly growing epidemic. The global prevalence of obesity is 13%, and more than a third of Americans are obese. Obesity is even more widespread in our local community. Over 40% of Duke patients are obese, and only a small number of them lose weight when followed longitudinally. Obesity poses a substantial threat to patient health, and is strongly associated with cardiovascular disease (CVD) risk factors (hypertension, diabetes, hyperlipidemia) as well as to CVD itself. Clearly, effective strategies to address the obesity epidemic on a population scale are needed to stem the growing burden of CVD. However, obesity is a heterogeneous disease; while some develop CVD early, others appear to be CVD resistant. This heterogeneity is reflected by the range of cardiometabolic abnormalities and CV events experienced by individuals with obesity. Similarly, responses to weight loss interventions in obese individual are also quite variable. While some lose weight and alleviate CVD risk factors, demonstrating apparent resilience to obesity and CVD risk, others do not respond to interventions. Thus, there is a clinical need to understand the mechanisms of successful weight reduction and CVD risk factor improvement in patients with obesity.

#### 1.2 Rationale

Understanding heterogeneity in weight loss and accompanying changes in CVD risk profiles at both epidemiological and biological levels is critical to providing personalized obesity care and to promoting CV health. In order to develop a complete picture of CVD resistance and resilience in obesity, we need to integrate all potential predictors to create a detailed map of individual clinical, behavioral, and molecular changes that occur in obesity. As recently advocated for by the National Institutes of Health in *JAMA*, this requires phenotyping large numbers of patients clinically, behaviorally, and physiologically, and integrating all of these data. Unfortunately, very few such data sources currently exist.

To accomplish this goal, we will identify a heterogeneous cohort of obese and normal BMI patients with high or low 10-year risk for CVD (i.e. >30% or <10%). We will then remotely collect data using electronic consents, electronic health record (EHR) clinical data, and online behavioral surveys. Further, we will collect biological data remotely with home biospecimen kits. Remote collection will reduce participant burden, increase participation and retention, and potentially reduce costs.

This platform will enable us to understand which clinical, behavioral, and biological markers are related to high-risk obese individuals vs. “resistant” low-risk obese and high-risk normal BMI individuals. Then, we will embed within this cohort a digital health behavioral intervention called TRACK. This will enable us to identify which clinical, behavioral, and biological markers change with weight loss, as well as which markers predict degree of weight loss and improvement in cardiometabolic risk factors (“resilience”).

One promising marker that we will specifically evaluate is branched chain amino acids (BCAA), which have previously been associated with insulin resistance in obese patients. We will assess whether BCAA are associated with CVD risk more strongly in obese compared with normal BMI patients, and whether BCAA predict response to a weight loss intervention. We will also perform metabolomic, genetic, and microbiome profiling for discovery science.

## **2. Objectives and Hypotheses**

Our primary objective is to understand a broad range of factors that contribute to the heterogeneity of CVD resistance and resilience among individuals with obesity at Duke. A secondary objective is to determine optimal methods of recruiting and consenting patients for clinical studies.

### **2.1. Primary Aims & Hypotheses**

Aim 1: CVD Resistance in Obesity. We aim to understand the clinical, behavioral, and biological factors associated with obesity and CVD risk by understanding differences between obese vs. normal BMI and high vs. low CVD risk groups. To do this, we will develop a cohort of obese and normal BMI patients at high and low CVD risk (n=600), and will deeply phenotype these individuals with behavioral data and biospecimen collection. Half (n=300) will also undergo CT testing to determine coronary artery calcium (CAC) score, for validation of the above associations. Finally, an embedded mechanistic study (n= 40) will explore the effect of the identified markers on vascular endothelial function.

Hypothesis 1a: BCAA are associated with CVD risk in obese individuals more than in normal BMI individuals in a real-world population, and this association will be validated with CAC score.

Hypothesis 1b: Specific clinical, behavioral, metabolomic, genetic, and microbiome profiles will be associated with CVD risk in obese individuals more than in normal BMI individuals.

Hypothesis 1c: In tissue-engineered blood vessels, BCAA interact with lipoproteins to induce endothelial dysfunction and increased monocyte/macrophage accumulation in the arterial wall, which are early markers of atherosclerosis.

Aim 2: CVD and Obesity Resilience. We will implement a proven, digital health behavioral intervention with 400 deeply phenotyped obese individuals in our cohort. We will then explore clinical, behavioral, and biological factors associated with heterogeneity in response to this intervention. Response will be defined as (1) weight loss and (2) changes in CVD risk factors, including LDL-cholesterol, HbA1c, Homeostasis model assessment for insulin resistance (HOMA), and hs-CRP.

Hypothesis 2a: Baseline clinical, behavioral, and/or biological markers, and specifically BCAA, will predict response to the intervention.

Hypothesis 2b: Biological markers, including BCAA and other markers discovered through integrated - omics analysis, will change from baseline with weight loss and changes in CVD risk factors.

Hypothesis 2c: Obese individuals with high CVD risk who lose weight with the intervention will develop biological profiles more similar to normal BMI, low CVD risk individuals.

